## Objectives

The objectives of this study include:

To assess the KAP among farmers and correlate it with respect to health-related Quality of Life (QoL) along with biochemical parameters.To conduct qualitative interview among farmers and respective stakeholders to develop need-based education intervention.To assess the impact of educational intervention on KAP and quality of life through multicentric RCT.

### Trial design

This study adopts a multi-phase, mixed-methods approach to address pesticide safety practices among farmers in Karnataka state. The study will be conducted in 4 different phases. Phase 1 is an analytical cross-sectional study, designed to evaluate the baseline knowledge, attitudes, and practices (KAP) of farmers using structured questionnaires. Phase 2 involves qualitative face-to-face interviews to gain deeper insights into the behavioural and contextual factors influencing pesticide usage and safety practices.

Phase 3 involves development and validation of need-based education module, where selection of experts will be carried out by purposive sampling technique. Phase 4 is a multicentric RCT, where 3 districts that includes 6 villages will be selected based on randomization. This study will be conducted as a two-arm, single-blind, parallel group with simple randomization of the districts and cluster randomization of farmers. The allocation ratio is 1:1, with one arm receiving the educational intervention and the other serving as a control group with no intervention. The outcomes will be assessed in terms of mean difference with the pre and post assessment in terms of KAP. The trial adopts a superiority framework [33] to assess the effectiveness of the educational intervention in improving pesticide safety knowledge, attitudes, and practices among farmers.

The below Fig. 1 depicts the trial process from recruitment to randomisation.

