**Methods:**

The study is a multicentric randomized controlled trial, which will be conducted across 4 phases in Udupi, Mysuru, and Shivamogga districts of Karnataka. Phase 1 features a cross-sectional study design of 175 farmers to evaluate their baseline knowledge, attitudes, and practices on usage of pesticides. Phase 2 employs semi-structured interviews with 20–30 farmers and 10–20 key stakeholders, including pesticide dealers, scientists from Farm Science Centers [Krishi Vigyan Kendra (KVK)], and joint directors of agriculture to explore pesticide handling approaches, challenges, and community-specific needs while handling pesticides. The findings from Phases 1 and 2 will help in development and validation of an intervention in the form of educational video in Phase 3 which will be piloted. Phase 4 involves implementing the validated intervention and conducting long-term follow-up to assess the impact and sustainability. Phase 4 will be a two-arm, single-blind, parallel-group randomized controlled trial, with villages randomized 1:1 into intervention and control groups. The intervention group will receive a 15–20-minute educational documentary in the local language, while the control group will receive no intervention. The outcomes will be evaluated based on changes in Knowledge, Attitudes, and Practices (KAP) scores, with assessments conducted immediately post intervention, at 6 months, and at 12 months from the date of intervention. These will be correlated with outcomes including quality of life and laboratory parameters.

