### Intervention

The primary component of the intervention will be a 15–20-minutes educational documentary in the local language. Topics like safe pesticide usage, proper storage, disposal methods, and associated health risks will be covered in this documentary. These elements will be presented through a story that will be displayed as a short documentary or movie among the farmers. Cluster sampling method will be utilised for selecting participants based on characteristics including age, education, and years of experience with pesticides or agriculture. The intervention will be provided in the intended villages at community centres or village halls.

The control group will not receive any educational intervention during the study period. Participation records will be maintained to track adherence to intervention, and any participant’s decision to withdraw from the study will be documented. If withdrawn, data collected up to the point of withdrawal will be retained for analysis. The appropriate reason will be documented for withdrawal if available.

To maintain the integrity of the study, participants will be requested to refrain from engaging in other pesticide-related educational initiatives, although they may continue their regular farming activities. Adherence to the intervention and pesticide practices will be monitored through regular follow-up calls, personal visits, and collaboration with field officers, community leaders, and local organizations.

The detailed participant timeline has been provided in Fig. 2, following the SPIRIT 2025 format [39] .

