In phase 4, the same villages from Phase 1 will be selected for recruitment. The districts will be randomized into control and intervention groups. Farmers will be identified using cluster sampling, with stratification based on age and agricultural experience. The intervention will be delivered to the experimental group at village halls or community centres. The cluster sampling approach ensures that participants are diverse in terms of age, educational level, and years of experience in agriculture allowing for a balanced representation across the groups.

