## Methods: assignment of interventions (for controlled trials)

### Random sequence generation and randomization

The allocation sequence will be generated using a computer-generated random number table through simple randomization. Participants who enroll in the study will be assigned with a unique identification code in alphabetical order. In Phase 4, villages will first be randomized into intervention or control groups. Within each group, participants will be categorized using a cluster randomization technique, accounting for confounding factors such as age, gender, education level, and agricultural experience. Stratification will further ensure balance by considering key variables like crop varieties and pesticide spraying techniques.

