### Statistical analysis

All data collected through the KAP and QoL questionnaires will be entered into SPSS version 20.0 (IBM, New York, NY, USA) for statistical analysis. Paired t-tests will be performed for continuous variables to compare pre- and post-intervention results. For improvements in quality of life and changes in laboratory parameters, the Wilcoxon Signed Ranks Test will be used. The results from the KAP surveys will be presented as mean ± standard deviation (SD). Qualitative interview data will be analysed using NVivo software, with thematic analysis to identify key patterns, insights and to understand the needs and perception of the farmers. Subgroup analyses based on confounding factors such as age, gender, and education level will be conducted to assess differential effects of the intervention. An intention-to-treat analysis will be performed and per-protocol analysis for participants deviating from the protocol.

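### Phase 4 allocates whole clusters, but the named tests and sample-size formula treat farmers as independent and do not compare the arms

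*Protocol article*

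**What the plan says.** **Allocation.** The abstract describes Phase 4 as a two-arm parallel trial "with villages randomized 1:1 into intervention and control groups". The section on random sequence generation agrees: "In Phase 4, villages will first be randomized into intervention or control groups". The section on recruitment says something else: "The districts will be randomized into control and intervention groups". The Trial design section also speaks of simple randomisation of the districts, with cluster randomisation of farmers.

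**Number of clusters.** Trial design: "Phase 4 is a multicentric RCT, where 3 districts that includes 6 villages will be selected based on randomization". This sentence is about how sites are selected, but it is the only place that gives the counts. The same section states: "The allocation ratio is 1:1, with one arm receiving the educational intervention and the other serving as a control group with no intervention".

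**Delivery.** The Intervention section: "The intervention will be provided in the intended villages at community centres or village halls".

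**Analysis.** The Statistical analysis section: "Paired t-tests will be performed for continuous variables to compare pre- and post-intervention results". For quality of life and laboratory parameters, "the Wilcoxon Signed Ranks Test will be used". Subgroup, intention-to-treat and per-protocol analyses are mentioned, but no other inferential test is.

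**Sample size.** Phase 4 is sized from a 12-farmer pilot that was itself a simple randomised trial, using a formula labelled as one for a paired t-test. The formula has no ICC, village size or design effect.

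**The concern.** On every reading of the article, groups of farmers are allocated together, never single farmers. Farmers in one village attend the same screening and may have other influences in common, so their changes in knowledge, attitude and practice (KAP) score are likely to be correlated. A test that counts each farmer as a separate piece of evidence then uses a standard error that is too small.

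A second problem lies in the same sentences. The paired t-test and the signed-rank test ask whether scores changed within a group of farmers. Neither asks whether the film arm changed more than the control arm, which is what a superiority trial has to show.

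What is at stake is the trial's main claim. A chance difference between a handful of villages could be reported as an effect of the film.

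**Working it through.** **Inputs from the article.** Six villages in three districts; 1:1 allocation; two-sided 5% (1.96); 80% power (0.84). The only quantitative sample size stated is 175 farmers, for Phase 1.

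**Inputs assumed.** The ICC of change scores: 0.01, 0.05, 0.10. Farmers per village, m: 29 (175/6, borrowed from Phase 1), with 10 and 45 as alternatives. Villages as the randomised unit, 3 against 3.

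**The plan's own figure.** The 5% is nominal. It is correct for these tests only if the ICC is zero; simulation at ICC 0 with m = 29 gave 5.1% for a two-sample t-test on change scores and 4.7% for a within-arm paired t-test.

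**Step 1: type I error of a farmer-level test.**

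Design effect DE = 1 + (m − 1) × ICC. Real error = 2 × [1 − Φ(1.96/√DE)].

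Example, m = 29 and ICC 0.05: DE = 1 + 28 × 0.05 = 2.40; √2.40 = 1.549; 1.96/1.549 = 1.265; two-sided tail = 0.206.

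| Farmers per village | ICC 0.01 | ICC 0.05 | ICC 0.10 |
|---|---|---|---|
| 10 | DE 1.09, 6.0% | DE 1.45, 10.4% | DE 1.90, 15.5% |
| 29 | DE 1.28, 8.3% | DE 2.40, 20.6% | DE 3.80, 31.5% |
| 45 | DE 1.44, 10.2% | DE 3.20, 27.3% | DE 5.40, 39.9% |

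**Step 2: does this hold for the test actually named?** The variance of a single arm's mean change is inflated by the same DE, so it should. Simulation with 3 against 3 villages, m = 29 and 10,000 runs:

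| Test | ICC 0.01 | ICC 0.05 | ICC 0.10 |
|---|---|---|---|
| Within-arm paired t-test | 8.1% | 20.3% | 31.5% |
| Two-sample t-test on change scores | 8.3% | 21.3% | 31.4% |
| t-test on village means, 4 df | 5.0% | 4.8% | 5.2% |

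**Step 3: power of the valid test.** Take the effect that independent farmers would detect with 80% power at 87 per arm (3 × 29): δ = √(2/87) × (1.96 + 0.84) = 0.425 SD. The standard error of the difference in village means, in SD units, is √[(2/3) × (ICC + (1 − ICC)/m)]. The test has 4 df (critical value 2.776).

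| ICC | Standard error | δ/SE | Power |
|---|---|---|---|
| 0.01 | 0.1715 | 2.48 | 47% |
| 0.05 | 0.2349 | 1.81 | 29% |
| 0.10 | 0.2956 | 1.44 | 20% |

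Even at ICC 0 it is 56%, because only six units carry the comparison.

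**Step 4: the other readings of the allocation unit.** If the three districts are allocated, the split is 2 against 1. The 1:1 ratio is then impossible and one arm has a single cluster, so variation between clusters cannot be estimated in that arm. If villages are paired within district, the three pairs leave 2 df instead of 4.

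**The case against.** **The figures rest on values that the article does not give.** This stands. There is no ICC and no Phase 4 village size; 29 borrows the Phase 1 total and 45 has no source. The relevant ICC is that of change scores, which may be small because stable differences between villages cancel. A reader might infer that the real error is far above 5% as a matter of fact. The documents do not support that: with 10 farmers per village and ICC 0.01 it is 6%. They support only the direction, for any positive ICC, and an illustrative range.

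**The named tests are within-arm, so a false-positive rate for comparing the arms describes a test the plan never names.** Partly right. Rejecting no change in one arm is not in itself a claim that the arms differ, and the missing between-arm test is a separate fault. Clustering inflates the within-arm test almost equally (step 2), so the independence problem remains.

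**Three villages per arm and 4 df may be the wrong count.** This stands as a condition. A reader might take 4 df as settled, but the article contradicts itself on the unit.

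**The detail may be in an analysis plan that is not shown.** Possible for a random effect or a df method. But the article does more than stay silent: it names specific tests and a sample-size formula that conflict with its own allocation.

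**Stratification and subgroup analyses may deal with it.** They do not. Balancing or subdividing by age, gender, education or experience leaves shared village effects in the standard error.

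**Conclusion.** The concern holds in a conditional form. As written, the analysis and the Phase 4 sample-size formula ignore the cluster allocation, and the named tests do not compare the arms. If change scores are positively correlated within villages, the type I error exceeds 5%. How far is unknown: about 6–16%, 8–31% or 10–40% with 10, 29 or 45 farmers per village, for assumed ICCs of 0.01 to 0.10 and six randomised villages. Confidence is high in the fault and its direction, and moderate in its size. It should be corrected before Phase 4 starts, because it bears on the trial's main claim.

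**What to change.** 1. Reconcile the abstract, Trial design, Recruitment and random-sequence sections so that one unit of allocation is stated. With three districts as the unit, a valid cluster-level comparison is hardly possible.
2. If villages are randomised, make the primary analysis a comparison between arms at that level. Either compare baseline-adjusted village means with a t-test on (villages − 2) df, or fewer if villages are paired within district; or fit a mixed model with a village random effect and Kenward-Roger or Satterthwaite df. The two need not agree exactly when village sizes differ. Keep the within-arm tests as description only.
3. Report the observed ICC with its uncertainty.
4. Restate the Phase 4 power with a stated ICC, village size and design effect, allowing for the few df, and consider more villages.
5. Do not rely on a permutation test with six villages. Its smallest two-sided p-value is 2/20 = 0.10 for 3 against 3, or 2/8 = 0.25 if paired within district.

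**Cost.** The change of analysis is wording and one model. The real cost is wider confidence intervals and a restated power well below 80%, roughly 20–47% under the assumed ICCs with 29 farmers per village. Recovering power means recruiting more villages, which adds fieldwork.

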**Fig. 1 Fig1:**
[figure not shown]
Flowchart depicting trial process from recruitment to randomisation

## Methods: Participants, interventions, and outcomes

### Patient and public involvement (PPI) – GRIPP2-SF

The study incorporates patient and public involvement (PPI) following the GRIPP2-SF (Guidance for Reporting Involvement of Patients and the Public – Short Form) [34], to ensure that the research is relevant, acceptable, and beneficial to the target population. Farmers will be involved to develop and validate the educational intervention based on their lived experiences with pesticide use. Farmers, agricultural officers, and community representatives will be engaged in the study, through focus group discussions to shape the study design, intervention content, and outcome measures. Their insights and experiences can help in the betterment of the mode of educational delivery and strategies to enhance adherence. During implementation, public representatives will be involved to support participant recruitment and provide feedback on intervention practicality. PPI members will also contribute to interpreting results, ensuring contextual relevance. Study findings will be disseminated through community meetings at village halls or community meetings. Reflections on PPI impact, including benefits and challenges, will be documented to develop future research.

### Study setting

The study will be conducted in 4 different phases. After a thorough literature review, it was evident that pesticide exposure and residue contamination were particularly high in certain regions of Karnataka. Data on pesticide exposure frequency were gathered from Farmer Producer Organizations (FPOs), which further supported the identification of high-risk areas. Additionally, factors such as crop diversification and regional agricultural practices were considered for study site selection. Based on these evidences, three districts—(a) Udupi, (b) Mysuru, and (c) Shivamogga— [31, 35, 36] were selected as the primary study sites. These districts have been reported to experience significant pesticide use, improper handling practices, and contamination risks in food and water systems. Prior studies have highlighted their vulnerability to pesticide-related health hazards, justifying their selection for this study. Furthermore, importance was given to interior villages within these districts to minimize contamination from external factors and focus on the specific challenges faced by the target group [31, 35, 36].

As a result, three districts that comprise various taluks were identified. Importance was given to interior villages in these taluks in order to minimize contamination and keep the study’s focus on the particular obstacles faced by the target group.

In-person field visits for data collection and laboratory investigations in these regions will be carried out. Additionally, permissions and ethical clearances from the appropriate authorities have already been obtained. In accordance with ethical guidelines, all participants will get a clear Participant Information Sheet (PIS) and Informed Consent (IC) form before enrolling to the study. The study complies with WHO and CONSORT 2025 guidelines and is registered with the Clinical Trials Registry India [CTRI] [37] with the registration number CTRI/2024/06/069678. The trial was registered on 28/06/2024 with the reference url https://ctri.nic.in/Clinicaltrials/regtrial.php? modid=1&compid=19&EncHid=55173.32324.

The study follows the SPIRIT 2025 guidelines [38] to ensure transparency and standardization. Details are provided in the supplementary file 1. Additionally, The SPIRIT 2025 figure format has been presented in Fig. 2 to illustrate the participant timeline and study procedures.

**Fig. 2 Fig2:**
[figure not shown]
SPIRIT Checklist 2025 for Timeline and Assessment Schedule of a Multicentric Randomized Controlled Trial on Impact of an educational intervention model on pesticide practices among farmers: A randomized controlled trial protocol in Karnataka, India

### Eligibility criteria

Inclusion criteria for study participants comprise: (a) Farmers who are actively engaged in regular pesticide spraying; (b) Farmers who are willing to provide informed consent (c) Farmers with a minimum of 5 years of experience in agriculture and pesticide spraying; (d) Farmers aged between 18 and 80 years, irrespective of their gender. Following this, any farmers who unwilling to provide consent and who are just involved in agriculture but lack pesticide spraying will be excluded from the study.

### Intervention

The primary component of the intervention will be a 15–20-minutes educational documentary in the local language. Topics like safe pesticide usage, proper storage, disposal methods, and associated health risks will be covered in this documentary. These elements will be presented through a story that will be displayed as a short documentary or movie among the farmers. Cluster sampling method will be utilised for selecting participants based on characteristics including age, education, and years of experience with pesticides or agriculture. The intervention will be provided in the intended villages at community centres or village halls.

The control group will not receive any educational intervention during the study period. Participation records will be maintained to track adherence to intervention, and any participant’s decision to withdraw from the study will be documented. If withdrawn, data collected up to the point of withdrawal will be retained for analysis. The appropriate reason will be documented for withdrawal if available.

To maintain the integrity of the study, participants will be requested to refrain from engaging in other pesticide-related educational initiatives, although they may continue their regular farming activities. Adherence to the intervention and pesticide practices will be monitored through regular follow-up calls, personal visits, and collaboration with field officers, community leaders, and local organizations.

The detailed participant timeline has been provided in Fig. 2, following the SPIRIT 2025 format [39] .

### Outcomes

The outcomes for this trial will be evaluated through quantitative and qualitative measures.

### Primary outcomes

The primary outcomes of the trial are (i) Knowledge, Attitude, and Practice (KAP) scores, assessed using a validated KAP questionnaire, and (ii) Quality of Life (QoL) scores, evaluated using the SF-36 Questionnaire. Both outcomes will be measured at baseline, post-intervention, and periodic follow-ups, with results analysed as mean changes over time and correlated with laboratory findings to provide a comprehensive understanding of the intervention’s impact.

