### Sample size

The sample size for each phase of the study was calculated distinctly, tailored to the study design and objectives. A formal power calculation was conducted to ensure appropriate statistical power for detecting meaningful differences.

For phase 1, the sample size was determined using data from Sam KG et al. (2007) [31], a study conducted in Udupi, Karnataka, India, which reported a baseline Knowledge, Attitude, and Practice (KAP) score of 30.88 with a standard deviation of 10.33. The required sample size was calculated using the following formula for comparing two means:

$$\mathrm{n}\;= \;2\times\;[(\mathrm{Z}_{\alpha/2}\;+\;\mathrm{Z}_{\beta})\;/\;\mathrm{Z}_{\delta}\;]^{2}$$ where, n = required sample size per group, Z_α/2_
**=** standard normal deviate for a given significance level (e.g., 1.96 for 5% significance level), Z_β_ = standard normal deviate for the desired power (e.g., 0.84 for 80% power), σ = standard deviation of the outcome variable (10.33 from prior study) and Z_δ_ = expected mean difference in the effect size.

A statistical power of 80% was chosen, which is widely considered an acceptable standard in health and social science research [40]. A power of 80% indicates that there is an 80% probability of detecting a true effect if one exists, while maintaining a Type I error (α) of 5%. Accounting for a 10% dropout rate, a total of 175 farmers will be selected using the stratified sampling method for the KAP assessment, quality of life evaluation, and laboratory investigations.

In phase 2, with approximately 20-30 farmers and 10–20 stakeholders from various villages across the selected 3 districts will be involved in the qualitative interviews for the need assessment phase.

Phase 3 focuses on the development and validation of the educational intervention by 6 experts from various domains including experts from agricultural sciences, pharmacy practice, community medicine, public health, and emergency medicine.

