For Phase 4, the sample size was determined based on findings from a pilot study involving 12 farmers, with equal allocation to intervention and control groups in a simple randomized controlled trial (RCT) design. The final sample size was calculated using the power calculation formula for a paired t-test:$$\mathrm{n}\;=\;2\times\;[(\mathrm{Z}_{\alpha/2}\;+\;\mathrm{Z}_{\beta})^{2}\;*\;2\sigma^{2}\;/\;\mathrm{Z}_{\delta}\:^{2}]$$, where, n = required sample size per group, Z_α/2_**=** standard normal deviate for a given significance level (e.g., 1.96 for 5% significance level), Z_β_ = standard normal deviate for the desired power (e.g., 0.84 for 80% power), σ = standard deviation of the outcome variable (10.33 from prior study) and Z_δ_ = expected mean difference in the effect size.

To ensure the effective implementation of the educational intervention, farmers will be stratified by age and education level.

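### Two primary outcomes at three post-baseline assessments, with no primary time point and no success rule, against a single-test 5% level

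*Protocol article*

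**What the plan says.** The Primary outcomes section lists two outcomes of equal rank: "i) Knowledge, Attitude, and Practice (KAP) scores, assessed using a validated KAP questionnaire" and "ii) Quality of Life (QoL) scores, evaluated using the SF-36 Questionnaire". It continues: "Both outcomes will be measured at baseline, post-intervention, and periodic follow-ups, with results analysed as mean changes over time".

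The Abstract (Methods) gives the schedule: "with assessments conducted immediately post intervention, at 6 months, and at 12 months from the date of intervention". It attaches these times to KAP and presents quality of life as something to be correlated with it. The Participant timeline section repeats the 6-month and 12-month visits. The Trial design section describes the outcome in terms of KAP alone.

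The Statistical analysis section gives paired t-tests for pre/post comparison of continuous variables and a separate Wilcoxon signed-rank test for quality of life. Neither is tied to a visit.

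The legend to the Phase 4 formula in the Sample size section takes the significance level as "standard normal deviate for a given significance level (e.g., 1.96 for 5% significance level"). That is the value for one test.

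**The concern.** A primary outcome should tell the reader which result, at which time, decides whether the intervention worked. Here two outcomes and three assessments stand level, with no statement on whether either outcome suffices or both are needed. Two things follow.

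First, if any one of several comparisons can be called the primary success, the chance of a false claim exceeds the 5% used in the Phase 4 formula.

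Second, the definition does not match the trial's purpose. The Background faults earlier programmes for raising knowledge and attitudes while doing less for behaviour, and blames short follow-up. The Conclusion names retention and change in behaviour over time as a key focus. Yet a rise in scores just after a 15–20 minute documentary would meet the primary definition as fully as a 12-month result. The trial could report primary success with nothing sustained, which is the weakness it sets out to correct.

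**Working it through.** **Inputs**

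- Primary outcomes: 2 (Primary outcomes section).
- Post-baseline assessments: 3 (Abstract, Methods). Applying all three to SF-36 combines this schedule with the Primary outcomes section, which says both outcomes are measured after the intervention and at follow-ups.
- Level: z = 1.96. Power: 80%, z = 0.84 (Phase 4 formula legend).
- Correlations between tests: not given. Assumed 0.5 to 0.8 between times and 0 to 0.7 between outcomes.

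**Step 1: the plan's own level.** 2 × (1 − Φ(1.96)) = 0.0500. This reproduces 5% for one test.

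**Step 2: number of tests.** One comparison with baseline per outcome per visit gives 2 × 3 = 6.

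**Step 3: independent tests.** Chance of at least one false positive = 1 − 0.95^k.

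| Comparisons that can each count as success | k | Chance |
|---|---|---|
| Two outcomes, one time | 2 | 9.75% |
| One outcome, three times | 3 | 14.3% |
| Two outcomes, three times | 6 | 26.5% |

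For two-sided tests on jointly normal statistics, independence is the worst case (Šidák), so 26.5% is a ceiling for six tests.

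**Step 4: correlated tests.** Six normal statistics were simulated with 1,000,000 draws per setting. The correlation matrix was the product of a between-outcome and a between-time component.

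| Between outcomes | Between times | Chance, 6 tests |
|---|---|---|
| 0 | 0.5 | 23.5% |
| 0.3 | 0.5 | 22.9% |
| 0.3 | 0.7 | 20.1% |
| 0.5 | 0.7 | 19.3% |
| 0.5 | 0.8 | 17.4% |
| 0.7 | 0.8 | 15.9% |

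The range is about 16% to 24%.

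**Step 5: cost of keeping more than one primary test.** With Bonferroni level α′ = 0.05/k, the sample size multiplies by [(z(1−α′/2) + 0.84) / (1.96 + 0.84)]², and power at the same size is Φ(1.96 + 0.84 − z(1−α′/2)).

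- Both outcomes at one named time, either sufficing: α′ = 0.025, z = 2.24. About 1.21 times the sample, or power of about 71%.
- All six tests: α′ = 0.0083, z = 2.64. About 1.54 times the sample, or power of about 56%.
- Both outcomes required at one named time: no split of the level is needed.
- One named primary test, then a fixed sequence: 5% at each step, no increase.

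Only ratios are given because the article states no Phase 4 sample size and no target difference.

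**The case against.** **Testing at each visit is never stated.** This is correct. The Primary outcomes and Statistical analysis sections imply it, so the count of six is an inference. No single longitudinal test is described, however. Even with one test per outcome, the chance is 9.75% if either may succeed and the tests are independent, and the article does not say whether either suffices.

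**A multiplicity rule may be in an analysis plan that is not shown.** This stands for the method of adjustment, whose absence is not the point. The choice of primary outcome and time point belongs in the protocol, and the Primary outcomes section sets out that definition and leaves it open.

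**Stronger readings a reader might infer, which the article does not support:**

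- *The trial breaks a stated 5% type I error.* The sentence "while maintaining a Type I error (α) of 5" per cent belongs to the Phase 1 survey. For Phase 4 the level appears only as an example value in a formula legend.
- *Knowledge, attitude and practice are three further primary tests.* With one SF-36 score that would make 12 tests and 46% if independent. The only KAP figure in the article is a single score ("which reported a baseline Knowledge, Attitude, and Practice (KAP) score of 30.88 with a standard deviation of 10.33"), and its SD is reused for Phase 4, which fits a total. Twelve tests would be an assumption.
- *Blood tests are wasted at the immediate visit.* The text does not place laboratory tests there, and the schedule figure is not available.
- *The immediate assessment falls minutes after the film.* This is plausible, but the Participant timeline section spreads implementation over 2 months, so the exact interval is not fixed.

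**The proposed remedy is one of several.** This is also correct. Step 5 lists others that would serve, provided a time point and success rule are named.

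**Conclusion.** The point holds in a limited form. The article leaves open which of two primary outcomes, at which of three assessments, decides the trial, and whether one or both must succeed. It sizes Phase 4 with a single-test 5% value. If six comparisons are made and any one counts, the chance of at least one false positive is at most about 26%, and about 16% to 24% under the assumed correlations.

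These percentages illustrate multiplicity only and are not this trial's actual error rate. They rest on the inferred count of six and on each test being a valid 5% test. They take no account of randomisation by village or of the use of within-person pre/post tests.

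The mismatch with the trial's purpose needs no such assumption: as written, an immediate gain ranks equally with a 12-month one. The definition should be tightened before results are known.

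**What to change.** In the Primary outcomes section, name one primary outcome and one time point that match the stated aim, for example total KAP score at 12 months, tested at two-sided 5%. Test SF-36 at 12 months only if KAP is significant, also at 5% (fixed sequence), and name the single SF-36 score used in that step. Make the immediate and 6-month results, the separate knowledge, attitude and practice scores, and the SF-36 domains secondary. Bring the Abstract and Trial design sections into line.

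The cost is a redrafted definition, with no added farmers or visits and no split of the significance level. The downside is that no quality-of-life claim can be made if KAP fails, and early gains become supporting evidence.

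Moving from the paired pre/post tests in the Statistical analysis section to a between-arm comparison would change the analysis itself. It is a separate issue and is not covered by this rewording.
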